### Trial objectives

The hypothesis of the trial is that consumption of high-selenium lentils from Saskatchewan, Canada, will reduce the body burden of arsenic and decrease arsenic toxicity in a chronically arsenic-exposed Bangladeshi population compared to those consuming low-selenium lentils.

The primary objective was to perform a double-blind, randomized controlled trial to determine whether incorporation of high-selenium lentils into the daily diet, providing at least the RDA of Se (55 ug), can decrease the body burden of arsenic, evident by higher excretion in urine and/or feces and decreased deposition in hair, compared to the treatment group on low-selenium lentil consumption. Secondary objectives were to determine if consumption of high-selenium lentils:improves antioxidant statusreduces oxidative DNA damagechanges acute phase proteins as well as serum lipid levels in arsenic-exposed individualsdecreases arsenic-related lung inflammation measured using exhaled nitric oxide as an indirect indicatorimproves the body mass index (BMI) and blood pressure of arsenic-exposed individuals

Herein, we describe the design and methods protocol for our 3-year study now underway.

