## Methods/design

This trial protocol has been approved by the University of Calgary’s Conjoint Health Research Ethics Board (Ethics ID: REB13-1211-Mod3), the University of Saskatchewan’s Biomedical Research Ethics Board (Bio-No. 14-212), plus the Research Review Committee, the Ethics Review Committee, and the Data and Safety Monitoring Board (DSMB) of the International Centre for Diarrhoeal Disease Research, Bangladesh (Icddr,b) (Protocol No. PR-14013). Any changes to the trial protocol are communicated to the relevant parties and ethics boards. The trial will be reported according to SPIRIT (Standard Protocol Items: Recommendations for Intervention Trials) 2013 [21] (see Additional file 1). A summary of the trial according to the WHO Trial Registration Minimal Data Set is provided in Table 1 [22].

**Table 1 Tab1:** WHO Trial Registration Minimal Data Set according to Moja et al*.* [22]

Data	Information
Trial identification number	ClinicalTrials.gov NCT02429921
Trial registration date	April 21, 2015
Secondary IDs	REB13-1211 (CHREB, University of Calgary), PR-14013 (ERC, icddr,b)
Funding sources	Global Institute for Food Security (GIFS); Grand Challenges Canada - Stars in Global Health Round 5
Primary sponsor	[name], Faculty of Vet. Med, University of Calgary, Canada
Secondary sponsor	RR, icddr,b, Dhaka, Bangladesh
Responsible contact person	RR, icddr,b; [contact]
Research contact person	[name], Faculty of Vet. Med., University of Calgary; [contact]
Brief title of the study	High-selenium Lentils Versus Arsenic Toxicity
Official title of the study	Mitigating arsenic toxicity in Bangladeshi people by supplementing their diets with high selenium lentils
Country of recruitment	Bangladesh
Health problem studied	Chronic arsenic poisoning
Intervention	High-selenium lentils, control: low-selenium lentils
Key inclusion and exclusion criteria	Inclusion criteria: families with >100 ppb As in their well water; ages eligible for study: 14–75
	Exclusion criteria: As content of well water ≤100 ppb; ill health detected during initial recruitment health check
Study type	Double blind, parallel, block-randomized, controlled intervention trial
Trial start date	September 28, 2015
Target sample size	200 per treatment group (400 in total)
Recruitment status	Active
Primary outcome	Arsenic body burden: We will determine if high-Se lentil consumption will decrease the body burden of As by measurement of As excretion in urine and feces and deposition in hair

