### Data analysis

Data are stored in a password-protected database at icddr,b, through a platform that allows sharing of data between project investigators (PIs) at icddr,b and the University of Calgary. Statistical analyses will be done using the statistical software SPSS for Windows PASW version 20. Normality and homogeneity of variances will be determined. Data not normally distributed will be transformed as necessary. Initially Spearman’s correlation analyses will evaluate univariate association between arsenic exposure (urinary and hair arsenic) and outcome variables (oxidative stress, antioxidant status, lung inflammatory status, and genetic variables). Covariates (e.g., demographic and socioeconomic variables, morbidity, daily diet, and BMI of participants) will be evaluated for significant association with exposure and outcomes. Missing data are excluded from that specific analysis. Significantly correlated variables will be further analyzed in multiple linear regression models controlling for potential confounding variables stratified by sex. Potential confounders will be identified based on correlations (*p* < 0.15) with the exposure (toxic metal) and outcomes and will be included in the final models when they change the effect estimate for metal exposure on the outcome by 5 % or more.

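### The stated analysis makes urinary and hair arsenic the exposure and names no comparison of the randomised arms, so as written it does not test the lentil effect

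*Protocol article*

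**What the plan says.** **Question the trial asks.** Under Trial objectives, the hypothesis is that high-selenium lentils "will reduce the body burden of arsenic and decrease arsenic toxicity in a chronically arsenic-exposed Bangladeshi population compared to those consuming low-selenium lentils". That section's main objective looks for a lower burden "evident by higher excretion in urine and/or feces and decreased deposition in hair, compared to the treatment group on low-selenium lentil consumption". Table 1 gives the primary outcome as whether high-selenium lentils "decrease the body burden of As by measurement of As excretion in urine and feces and deposition in hair". The Sample size section uses mean hair arsenic in a control and a selenium group. The Discussion expects a significant fall in body burden in the high-selenium group and calls that burden the primary outcome.

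**Analysis the article describes.** The Data analysis section starts with Spearman correlations that "will evaluate univariate association between arsenic exposure (urinary and hair arsenic) and outcome variables". The other side of these correlations is "outcome variables (oxidative stress, antioxidant status, lung inflammatory status, and genetic variables"; no arsenic measure is among them. It continues: "Significantly correlated variables will be further analyzed in multiple linear regression models controlling for potential confounding variables stratified by sex". Confounders are screened at p < 0.15 and kept if they move the estimated effect of metal exposure by at least 5%. Morbidity and BMI are among the named covariates. The section does not mention treatment group, lentil type or any between-group test.

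**The concern.** A randomised trial earns its causal claim by comparing the groups that were randomised. The Data analysis section sets out the method of an observational study of arsenic and biomarkers: correlate, screen, then adjust for confounders by change in estimate. The primary outcome takes the role of explanatory variable, and the lentil arm has no role at all.

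Two further role changes follow.
- Under Trial objectives, higher urinary arsenic is evidence of benefit, because more is excreted. In Data analysis the same variable stands for a higher toxic exposure.
- Morbidity belongs to the major outcome in the abstract, and BMI is a secondary objective. In Data analysis both are candidate confounders, so a model could adjust for what the lentils are meant to change.

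At stake is whether the confirmatory conclusion rests on the randomisation. The Discussion intends to take the results to government as advice on lentil imports.

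**Working it through.** **1. The test the trial was sized for.** Inputs from the Sample size section: means 2.01 and 1.23 μg/g, SDs 1.4 and 0.73, one-sided type I error 0.05, power 0.80.

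n per arm = (SD₁² + SD₂²)(z₀.₉₅ + z₀.₈₀)² / δ², with δ = 2.01 − 1.23 = 0.78

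= (1.4² + 0.73²)(1.645 + 0.842)² / 0.78² = 25.3, rounded up to 26.

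This is the stated 26 per group. The two-sided version gives 33. The planned test is therefore a one-sided, two-arm comparison of mean hair arsenic.

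**2. The sections side by side.**

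| Item | Objectives, Table 1, Sample size, Discussion | Data analysis |
|---|---|---|
| Explanatory variable | Lentil arm | Urinary and hair arsenic |
| Urinary and hair arsenic | Primary outcome | Exposure |
| Fecal arsenic | Primary outcome | Not mentioned |
| Morbidity, BMI | Outcomes (abstract; Trial objectives) | Covariates, candidate confounders |
| Effect estimated | High- versus low-selenium difference | Metal exposure on outcome |

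Of the three primary measures, none is a dependent variable in Data analysis.

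**3. Illustration that the two analyses answer different questions.** Assumptions: 200 per arm, independent normal data, two-sided 0.05, 4000 simulated trials per case, arsenic measured on treatment. The 0.3 correlation below is assumed. The arm effect of 0.70 SD is 0.78 divided by the root-mean-square SD, √((1.4² + 0.73²)/2) = 1.116.

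| Case | Spearman test, arsenic with biomarker, significant | Arm comparison of arsenic, significant |
|---|---|---|
| No arm effect; arsenic-biomarker correlation 0.3 | 100% | 4.8% |
| Arm effect 0.70 SD; no arsenic-biomarker correlation | 5.3% | 100% |

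The correlation test is positive when the lentils do nothing, and stays at its chance rate when they work as the sample size assumes. The simulation ignores household clustering, so these percentages are not the trial's power. They show only that the stated test carries no information on the hypothesis.

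**The case against.** The strongest reply is that a journal article condenses the full protocol, and an unseen analysis plan may contain the arm comparison. Between-arm intent is plain in the objectives, the sample size and the Discussion. Data analysis does not claim its list is complete, and its check of homogeneity of variances would suit group comparisons, although it suits regression equally. Relating arsenic to oxidative stress or lung inflammation is also a sensible secondary question, since the hypothesis covers toxicity, and in that question arsenic does belong on the explanatory side.

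Much of this stands. A reader might infer that the arms will never be compared; the documents do not show that. Nor is it a finding that lipids, blood pressure or acute phase proteins have no stated model, because an article commonly leaves that to the analysis plan.

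The reply does not remove the point. The section does not merely stay brief: it sets out a specific procedure, down to a p-value screen and a 5% rule, and gives two primary measures a role that conflicts with Table 1. It does not label this work secondary. An analysis plan that compared the arms would differ from this text, so the text needs correcting either way.

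**Conclusion.** The point holds for the stated analysis and should be corrected before any results are seen by arm. As written, Data analysis gives no estimate or test of the high- versus low-selenium difference for any of the three primary measures. The conclusion rests on the wording of the sections; the simulation only illustrates it. No sample size changes.

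Three stronger readings are not supported.
- A reader might infer that the regressions condition on a variable measured after randomisation. The section gives no visit for the arsenic value, and urine and hair are both collected at baseline. The objection applies only if 3- or 6-month values are used. With baseline values the analysis still yields no treatment effect.
- A reader might infer selective reporting from carrying forward only significantly correlated variables. The text says which variables enter regression; it does not say that null results will be withheld.
- A reader might wish to credit the correction with a stated gain in precision. Baseline adjustment usually helps, but the documents give no baseline-to-follow-up correlation from which to size it, and it is a separate improvement.

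**What to change.** Rewrite the Data analysis section, and align any analysis plan, as follows.

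1. **Lead analysis:** a comparison of high- versus low-selenium groups, as randomised, on the primary arsenic measures. 6-month hair arsenic is the measure the trial was sized on; urinary and fecal arsenic are also analysed as outcomes. If one of the three is to be the sole primary measure, the sponsor should decide and say so. Stool comes from only about 40 participants, so the fecal estimate will be imprecise.
2. **Model:** a linear mixed model with arm and the baseline value of the measure as fixed effects, and household as a random effect, because Randomization and blinding assigns lentils by household.
3. **Keep the arm comparisons free of the screening rules:** they should not depend on the significant-correlation step or on change-in-estimate confounder selection, and should not adjust for post-baseline morbidity or BMI.
4. **Exploratory work:** keep the Spearman correlations and metal-exposure regressions under that label, and state which visit's arsenic value they use.

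The cost is rewording. Every measurement needed is already planned and standard mixed-model procedures suffice. The article reports that recruitment is under way and that investigators do not know the lentil type, so the change can be fixed in advance. It does not by itself settle missing data: a participant lacking the day-1 or 6-month hair sample would still drop out of the hair model as described.

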**Methods/design:**

A total of 400 participants (about 80 families) will be divided into two groups via computer-generated block randomization. Eligibility criteria are age (≥14) years) and arsenic concentration in the household tube well (≥100 ppb).

In this double-blind study, one group will eat high-selenium lentils grown in western Canada; the other will consume low-selenium lentils grown in Idaho, USA. Each participant will consume 65 g of lentils each day for 6 months. At the onset, midterm, and end of the trial, blood, urine and stool, plus hair (day 1 and at 6 months only) samples will be collected and a health examination conducted including assessment of acute lung inflammation, body mass and height, and blood pressure. The major outcome will be arsenic excretion in urine and feces, as well as arsenic deposition in hair and morbidity outcomes as assessed by a biweekly questionnaire. Secondary outcomes include antioxidant status, lipid profile, lung inflammation status, and blood pressure.

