Key secondary outcomes	We will determine if high-Se lentils:
	1. Increase concentrations of protective antioxidants and reduce oxidative stress and acute phase response in blood
	2. Modulate serum lipid profile and blood pressure
	3. Reduce As-related lung inflammation

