## Discussion

This trial is the first to use a high-selenium food source, i.e., lentils, in an attempt to combat the adverse health effects of chronic arsenic poisoning. Since lentils are an excellent source of non-animal protein and micronutrients such as Zn and Fe [35], we expect to see an improved BMI after 6 months of supplementation and possibly improved overall health status in all participants of the trial, regardless of the selenium content of the lentils. As a result, some of the proposed biomarkers may not be significantly different between the control and the high-selenium groups. However, since selenium can form a complex with arsenic, selenium supplementation, in principle, can reduce arsenic toxicity. We expect to see a significant decrease in the body burden of arsenic, the primary outcome of this study, in the high-selenium group. Mild beneficial effects of selenium have been indicated in a number of supplementation trials with selenium alone or in combination with other micronutrients [36–38]; more trials are needed for conclusive evidence.

If we can prove that health benefits occur due to consumption of high-selenium lentils in arsenic-exposed communities, the first step will be to inform the Bangladeshi public — through a follow-up meeting with the participants and local media — and to promote consumption of higher-selenium food sources. Here again, the female family head will be the one responsible for purchasing and preparing nutritious food for the family.

Furthermore, we will disseminate the study results to the Food Planning and Monitoring Unit (FPMU) of the Ministry of Food, the Government of Bangladesh, and provide evidence-based advice for policy formulation on lentil import and agricultural aspects. The results may guide Bangladeshi importers to specifically target importation of high-selenium lentils.

The long-term goal toward food security will entail working on agronomic techniques to increase the production of high-selenium lentils in Bangladesh.

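### The outcome list in the Data analysis section does not match the stated secondary outcomes: lipids, blood pressure and acute phase proteins are absent, BMI is only a covariate, and undefined genetic variables are added

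*Protocol article*

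**What the plan says.** The secondary objectives under Trial objectives cover seven measures in five bullets. Two bullets hold two measures each: one concerns "acute phase proteins as well as serum lipid levels in arsenic-exposed" people, the other "the body mass index (BMI) and blood pressure of arsenic-exposed individuals". The remaining three concern antioxidant status, oxidative DNA damage and lung inflammation.

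Table 1 gives three key secondary outcomes. The second is "Modulate serum lipid profile and blood pressure", and the first includes the acute phase response. The Abstract states: "Secondary outcomes include antioxidant status, lipid profile, lung inflammation status, and blood pressure".

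The Data analysis section opens with a correlation step: "Initially Spearman’s correlation analyses will evaluate univariate association between arsenic exposure (urinary and hair arsenic"). What arsenic is to be correlated with is given in a parenthesis that differs from the lists above: "outcome variables (oxidative stress, antioxidant status, lung inflammatory status, and genetic variables"). The sentence after that gives BMI another role: "Covariates (e.g., demographic and socioeconomic variables, morbidity, daily diet, and BMI of participants) will be evaluated". The regression step that follows estimates the effect of metal exposure on the outcomes.

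**The concern.** The Data analysis section is the only place in the article that says which variables are analysed and how. Its outcome list has no e.g., whereas the covariate list in the next sentence has one, so it reads as complete. Followed as written, lipids, blood pressure and acute phase proteins are collected but never analysed as outcomes, BMI is used to adjust other results, and an item that the trial never describes is analysed.

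Two things are at stake. Until the lists are reconciled, which measures count as secondary outcomes can be settled after the data are seen. And the secondary objectives ask what high-selenium lentils do compared with low-selenium lentils, while the section relates outcomes only to arsenic in urine and hair. Even the listed outcomes would then not be answered by the randomised comparison.

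**Working it through.** The plan gives no figure on this point, so the check sets the lists side by side. The Measured column draws on Study procedures and Laboratory methods.

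| Measure | Trial objectives | Table 1 | Abstract | Measured as | Role in Data analysis |
|---|---|---|---|---|---|
| Antioxidant status | bullet 1 | yes | yes | GSH/GSSG | outcome |
| Oxidative DNA damage / oxidative stress | bullet 2 | yes | no | 8-OHdG | outcome |
| Acute phase proteins | bullet 3 | yes | no | Hs-CRP, AGP | absent |
| Serum lipids | bullet 3 | yes | yes | triglyceride, total cholesterol, HDL, LDL | absent |
| Lung inflammation | bullet 4 | yes | yes | exhaled nitric oxide | outcome |
| BMI | bullet 5 | no | no | height, weight | covariate only |
| Blood pressure | bullet 5 | yes | yes | blood pressure | absent |
| Genetic variables | no | no | no | no assay named | outcome |

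Counts from the table:

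- Trial objectives by measure: 7 − 3 = 4 not listed as outcomes (acute phase proteins, lipids, BMI, blood pressure), so 4/7 = 57%.
- Trial objectives by bullet: bullets 3 and 5 are wholly absent, so 2/5 = 40%.
- Table 1 by measure: 6 − 3 = 3 absent. Item 2 is missing entirely, item 1 is covered except for the acute phase response, and item 3 is covered.
- Abstract: 4 − 2 = 2 absent (lipids, blood pressure).

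The missing outcomes have not been dropped from the trial. Blood pressure, height and weight are taken at baseline, 3 months and 6 months. Blood is drawn at the same visits, and Laboratory methods describes the lipid and acute phase assays.

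**BMI.** The section does not say which visit's BMI serves as a covariate. Any candidate confounder enters a model if it passes a correlation screen (p < 0.15) and shifts the exposure estimate by at least 5%. BMI measured after randomisation could be affected by the lentils, and adjusting for it could remove part of the effect that the trial is meant to estimate. Baseline BMI has no such problem. Morbidity has a similar double role (a major outcome in the Abstract, a covariate here), but it is not a secondary outcome and is not counted above.

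**Genetic variables.** The nearest trace is the storage of buffy coat cells in RNAlater under Study procedures. No assay, variable or objective is attached to it.

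**Comparison made.** Both steps in the section, the Spearman correlations and the regressions, take arsenic as the explanatory variable. The lentil group appears in neither, so adding the missing outcomes to the list would not by itself answer the secondary objectives.

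**The case against.** The best defence is that the parenthesis belongs to an initial correlation step and was never meant to define the secondary outcomes. The article is condensed, and a statistical analysis plan that is not shown may analyse every outcome by lentil group. This stands as a limit: nobody can say from the article that the omitted outcomes will go unanalysed. It does not remove the conflict, because the list as printed still disagrees with the article's own Table 1 and objectives.

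It is also fair that the Abstract and Table 1 do not contradict the Trial objectives by being shorter. The Abstract says that the secondary outcomes include certain items, and Table 1 is labelled as key outcomes. The real mismatch is between the Data analysis section and the other three.

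Four stronger readings are tempting and are not supported:

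- *Most secondary questions go unanswered.* This holds only by measure (4 of 7). By objective it is 2 of 5, and by the Abstract 2 of 4.
- *Genetic variables cannot be an outcome because genotype is fixed.* The article does not say genotype. Cells kept in RNAlater are compatible with gene expression, which could change. Undefined is as far as the text goes.
- *The Discussion contradicts the BMI objective, so BMI should become descriptive.* The Discussion says "we expect to see an improved BMI after 6 months of supplementation and possibly improved overall health status in all participants of the trial", whichever lentil they eat. It does not say that the gain will be equal in the two groups, and a further effect of selenium remains possible.
- *The mismatch inflates false positives.* The number of secondary tests is a separate matter that is commonly left to the analysis plan, and the aligned list would contain no fewer measures.

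**Conclusion.** The point holds as an internal contradiction that should be reconciled. Of the seven secondary measures in the Trial objectives, three (lipids, blood pressure, acute phase proteins) are absent from the Data analysis section and one (BMI) is there only as a covariate. One undefined item is added. The outcomes that are listed are tied to arsenic exposure and not to the randomised group.

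This rests on two readings: that the outcome list is complete as printed, and that oxidative DNA damage is covered by oxidative stress, which fits the use of 8-OHdG in Laboratory methods. A separate analysis plan could settle what is done in practice, but the article would still need correcting. The point concerns the secondary outcomes only.

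**What to change.** In the Data analysis section:

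1. Replace the parenthesis with the Table 1 secondary outcomes (antioxidant status, oxidative stress, acute phase proteins, lipid profile, blood pressure and exhaled nitric oxide), plus BMI as in the Trial objectives.
2. State that each is compared between the randomised lentil groups at 6 months, and keep the correlations and regressions on arsenic exposure as exploratory.
3. State that BMI measured after randomisation is not a confounder in those comparisons. Baseline BMI may be a covariate.
4. Define the genetic variables (what is measured, in which sample, for which objective) or remove them from the outcomes.

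No extra sampling or assay is needed for the omitted outcomes. The cost is a small amount of added analysis, since a group comparison for each outcome goes beyond what the section now describes.

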### Sample size

We determined the sample size for this trial with an online power and sample size calculator (www.powerandsamplesize.com), based on a one-sided effect for arsenic concentration in hair.

Based on a previous intervention trial [28], in which arsenic-exposed participants received selenium-enriched yeast (100–200 μg/day, an amount two to four times higher than our dietary treatments), we calculated the sample size from their data generated after a 9-month intervention. Using the mean arsenic levels in hair of the control and selenium-treatment groups, Mean_A_ = 2.01 μg/g (±1.4) and Mean_B_ = 1.23 (±0.73), respectively, and a type I error of 0.05 and a power of 0.80, we calculated a minimum participant number of 26 per treatment group. This sample size underestimates our needed sample size due to substantial differences from our planned trial. Considering the up to fourfold lower selenium treatment in our trial, we felt it was prudent to quadruple the number (=100) and then double it to accommodate our larger age range, shorter duration, and loss to follow-up, arriving at the final participant number of 200.

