**Fig. 1 Fig1:**
[figure not shown]
Flow chart of the dietary intervention trial; BMI, body mass index; BP, blood pressure; HHs, households

At baseline (day 1), midterm (3 months), and at the end of the study (6 months), samples will be collected as described in the following paragraph.

Urine (15–20 ml) will be collected in trace-element free tubes, aliquoted, and stored at –80 °C. Stool samples (5–10 g) will be collected in trace-element free tubes from a subset (about 40) of participants and stored at –20 °C. Blood (10 ml/visit) will be collected in trace-element free tubes (S-Monovette®, Sarstedt). Blood samples, in cool boxes, will be sent to the Dhaka Lab on the same day for separation into plasma and cells, and aliquots of plasma will be stored at –80 °C. Buffy coat cells will be stored in an RNAlater freezer at –80 °C. Whole blood (100 μl) will be stored at –80 °C. Hair will be collected from the back of the head, close to the nape of the neck (approximately 0.2 g) for analysis of arsenic.

Samples may be stored for up to 5 years for future analyses.

The following physical examinations will be performed at baseline, midterm, and end of study:Height and weight are measured to calculate body mass index (BMI).Blood pressure (BP) is tested because of the association between arsenic and hypertension [29].Lung inflammation (NIOX MINO®) — study participants exhale into a machine which detects exhaled nitric oxide, a marker for eosinophilic airway inflammation [30]. Previous reports showed an association of arsenic exposure with respiratory effects and inflammatory response of airway cells [31, 32].

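### Excluding missing values analysis by analysis leaves 3-month data of later dropouts unused in 6-month group comparisons of urine, blood, lung, BMI and blood-pressure outcomes

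*Protocol article*

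**What the plan says.** The Data analysis section states: "Missing data are excluded from that specific analysis". No other sentence in the article deals with missing values. The methods named there are Spearman correlations and then "multiple linear regression models controlling for potential confounding variables stratified by sex". Candidate covariates include "demographic and socioeconomic variables, morbidity, daily diet, and BMI of participants", and they are retained model by model according to their correlations and how far they shift the metal-exposure estimate.

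On timing, Study procedures says "At baseline (day 1), midterm (3 months), and at the end of the study (6 months), samples will be collected", and height, weight, blood pressure and exhaled nitric oxide follow the same three visits. Two samples differ. Stool comes "from a subset (about 40) of participants". The Abstract limits hair: "plus hair (day 1 and at 6 months only) samples will be collected". Study procedures lists hair under the three-visit sentence without that limit, so the two places should be reconciled.

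Table 1 defines the primary outcome through "measurement of As excretion in urine and feces and deposition in hair". The Sample size section expects some loss, since its last step is to "double it to accommodate our larger age range, shorter duration, and loss to follow-up". It gives no dropout rate.

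**The concern.** The exclusion rule is stated, so it is open to comment even though further detail may sit in an analysis plan that is not shown. A plan that follows the sentence inherits case deletion.

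Most outcomes have two follow-up measurements. A regression on the 6-month value that excludes anyone without that value ignores what the same person's 3-month value says about it. Two things are at stake. One is precision. The other is validity: deletion is unbiased under a stricter assumption than a likelihood-based repeated-measures model, which also tolerates loss that depends on values already observed. A larger sample restores precision but does not remove selection bias.

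Because covariates are chosen separately for each model, two outcomes from the same trial may also rest on different subsets of the randomised participants.

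**Working it through.** **The plan's own figure.** The article gives no missingness rate to reproduce, but the sample size that absorbs the loss can be checked. Inputs from Sample size: means 2.01 and 1.23, SDs 1.4 and 0.73, one-sided type I error 0.05, power 0.80.

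n = (1.4² + 0.73²) × ((1.645 + 0.842)/0.78)² = 25.33, rounded up to 26 per group, as stated. Then 26 × 4 = 104, taken as 100, and doubled to 200. The doubling covers three reasons together, so the share meant for dropout cannot be recovered.

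**Precision lost in a 6-month comparison.** Assumptions, because the article gives none of these:
- a fraction d is missing at 6 months, and everyone is seen at 3 months;
- ρ is the correlation between the 3- and 6-month values;
- the effect is set so that 200 per group has 80% power one-sided, that is √(2/200) × (1.645 + 0.842) = 0.249 SD;
- participants are treated as independent.

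Exclusion leaves 200(1 − d) per group. Using the 3-month value gives an effective n of 200(1 − d)/(1 − dρ²). For example, with d = 0.20 and ρ = 0.5, this is 160/(1 − 0.20 × 0.25) = 168.

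| Dropout | n and power, exclusion | Effective n and power using 3 months, ρ = 0.5 to 0.8 | Gain in power points |
|---|---|---|---|
| 10% | 180, 76.2% | 185 to 192, 77.2% to 78.6% | 1.0 to 2.4 |
| 20% | 160, 71.9% | 168 to 183, 73.8% to 76.9% | 1.9 to 5.0 |
| 30% | 140, 66.8% | 151 to 173, 69.8% to 74.8% | 3.0 to 8.0 |

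Anyone lost before 3 months has no midterm value to use, so these gains are on the high side. For hair, with no 3-month sample, the gain from this source is zero.

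**Bias.** A simulation assumed no true effect and 20% dropout in each arm. Dropout was completely random in one arm and more likely with a high 3-month value in the other. Exclusion gave a spurious 6-month difference of −0.08 SD (ρ = 0.5) or −0.12 SD (ρ = 0.7). Using the 3-month value gave 0.003 and −0.001 SD, effectively zero. This shows that the bias can occur, not that it will.

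**Loss through covariates.** Assume 5% to 20% lost by 6 months, and 1% to 2% missing independently on each of five covariates.
- Best case: 0.95 × 0.99⁵ = 0.903 kept; 400 × (1 − 0.903) = 39 discarded.
- Worst case: 0.80 × 0.98⁵ = 0.723 kept; 400 × (1 − 0.723) = 111 discarded.

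A five-covariate model would therefore keep about 72% to 90% of 400.

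**The case against.** The strongest reply is that the exclusion sentence sits among exposure-outcome steps: correlations of urinary and hair arsenic with biomarkers, then regressions whose confounders are judged by their effect on the metal estimate. A reader might infer that a missing covariate removes a participant from the trial's treatment comparison. The section describes no covariate-adjusted comparison of the arms, so that is only what would follow if the rule were carried over. This stands, and the point is worded conditionally for that reason.

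A reader might also infer that midterm data are wasted altogether. They are not. Exclusion applies to the specific analysis, so a later dropout's 3-month values remain usable in any 3-month analysis, and the text does not say which visits enter the regressions.

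Nor does the point reach hair arsenic, the endpoint that sized the trial. With a single follow-up value, a baseline-adjusted complete-case analysis and a likelihood model give nearly the same answer under missing at random.

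It is tempting to add that people who stop eating the lentils are the likeliest to be missing. Nothing in the article supports this. Not eating the lentils is different from missing a measurement, and Interventions and compliance provides weekly distribution and weekly questionnaires, with twice-weekly visits in the first month. Blinding also makes arm-dependent dropout less likely, without ruling it out.

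Finally, the sample size makes some allowance for lost numbers. That answers part of the precision argument and none of the bias argument.

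**Conclusion.** The point holds in a limited form. The only stated rule is exclusion per analysis, no repeated-measures model is named, and most outcomes, including urinary arsenic within the primary outcome, have a 3-month value that a 6-month analysis under this rule would ignore.

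The likely cost in precision is small: a few power points at 10% to 20% dropout. The stronger reason to change is that the named method is unprotected against dropout that depends on earlier values differently by arm, and protection is cheap. Every size given here rests on assumed dropout, correlation and covariate-missingness figures, and the power figures ignore clustering by household. The conclusion does not cover hair, unless reconciling the two descriptions of hair sampling shows that a 3-month sample is taken.

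**What to change.** For comparisons of the randomised groups, replace the exclusion sentence with the following.

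- Outcomes measured at 3 and 6 months: a likelihood-based linear mixed model using all available visits, with group-by-visit terms and a household random effect, since households are the randomised unit.
- Hair arsenic: a baseline-adjusted 6-month model with a household effect.
- Missing baseline covariates: keep the participant in the randomised comparison, using a simple mean or indicator fill. Confine this to that comparison. In the exposure-outcome models it could leave residual confounding, and morbidity, diet and BMI there may be measured after baseline.
- Sensitivity: report the complete-case result alongside, with one departure-from-MAR check for hair arsenic.

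The text should also say which analyses any remaining exclusion rule covers. The cost is wording and a little more analysis work. No new data are needed, and the named software fits mixed models. Trial status reports that recruitment is still under way, so the change can be made before the outcome data are analysed.
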